### Intervention

The UPLIFT intervention description is per the TIDieR (template for intervention description and replication) statement.^27^ All intervention is consistent with usual care as recommended in the Australian Living Clinical Practice Guidelines.^28^ There are three session foci: (1) upper limb motor impairment (eg, target strength, control, coordination and flexibility) and functional task (eg, stabilisation, reach, grasp, manipulation and release) training to maximise transition to real-world use; (2) language impairment (ie, production at the word, sentence and conversational level in comprehension and speech) and communication in context (functional communicative effectiveness in relevant everyday situations through multiple modalities such as gestures, speech and writing) training; and (3) integrated upper limb and language impairment and functional training to maximise the potential for therapeutic synergy (synchronously/asynchronously). Session content is individually tailored to each participant based on their goals (4 weeks, 3 months and dream, ie, no time limit) and daily routines (upper limb and language use during a typical day) that are established in Week 0 Session 1. Content is adapted within and between sessions to ensure optimal challenge based on a participant’s daily performance and to maximise and maintain engagement. In the first session, the participant and treating therapist discuss the participants usual upper limb and language daily routines (from waking up through to going to bed, probing how the upper limb or language is used in all activities) and establish goals (4 weeks/3 months/dream). Materials are consistent with a standard outpatient rehabilitation facility and include access to training equipment, electrical stimulation units, height adjustable bed and table. We do not use any robotic devices. Participants in the severe strata receive intervention in person at a university or health clinic, while the mild-moderate strata receive all intervention via telerehabilitation (Zoom) in a setting with appropriate internet and safety set-up, for example, quiet space in their home. Over 4 weeks, a minimum of 20 (of total 80) sessions each of upper limb, language and integrated treatment are provided, leaving 20 flexible sessions, for example, to participant’s goals or staffing availability. Dose within each session is reported in real-time using a custom-built repeated instrument REDCap form consistent with a multidimensional dose articulation framework.^29^
Table 2 describes how all dose dimensions are applied and measured within the UPLIFT protocol. Participants can do up to 2 hours/week of upper limb and/or language therapy intervention outside UPLIFT. A small amount of concomitant therapy is allowed to ensure participants do not lose access to services because of trial participation. All UPLIFT intervention is provided by physiotherapists, occupational therapists, speech pathologists or allied health assistants who are trained in study procedures (ie, study protocol, dose recording, adverse event reporting) via review of written and audiovisual materials, and attendance at a virtual training session.

**Table 2 T2:** Multidimensional dose articulation framework dimensions

Item	Dose dimension	UPLIFT protocol
1	Duration	Completion within a minimum of 4 weeks and maximum of 5 weeks.
2	Days	Monday to Friday; minimum 20 weekdays, maximum 25 weekdays to allow for, eg, public holidays, medical appointments, staff illness.
3	Sessions	Four sessions/day. Focus on upper limb, language or integrated content.
4	Session length	30 min if 2 hours/day or 60 min if 4 hours/day.
5	Session density	Ratio of time-on-task to time-off-task.
6	Episode(s) length	Equates to a task completed and how long for, ie, time-on-task Time on task **includes**: Successful/unsuccessful repetitions Appropriate rest to recover between repetitions or sets Task demonstration Task-related instructions Task-related feedback Weekly assessments Time on task **does not include**: General conversation (unless language task) Set-up of environment where participant is not engaged Transfers not related to the task Scheduling of appointments Discussing previous sessions or post-session effects Toilet breaks Scheduled rest or time off task >2 mins Adverse event discussions Telehealth technical issues, eg, connection issues
7	Episode(s) difficulty	Consistent ratings used for all episodes of all sessions. **Level A**: Consistent reliance on supports to complete task. **Level B**: Require support to complete the task more often than not. **Level C**: Mostly independent in task completion. **Level D**: Mostly independent in task completion with challenges added. Support examples: gravity-eliminated, electrical stimulation. Challenge examples: load, gravity, speed.
8	Episode(s) intensity	Successful repetitions, unsuccessful repetitions, summed total repetitions. Task goal, eg, wrist extension to target. Successful repetitions: any attempt that meets the task, eg, wrist extension to reach the target. Unsuccessful repetitions: any repetition less than the task, eg, wrist extension that did not reach the target. Total repetitions: summed successful and unsuccessful repetitions.

UPLIFT, UPper limb and Language Impairment and Functional Training.

### Fidelity

All data are entered into a custom-built electronic case record form in REDCap and checked remotely (goal within two working days) by UPLIFT central staff. Site-specific staff address all data queries. A file note with reason(s) is included in REDCap whenever a session is >10% shorter than the target dose (ie, <27 min for 30 min session or<54 min for 60 min session) or if technical issues arise during telerehabilitation. The entirety of two intervention days (10% of duration) are video-recorded (Zoom): Week 0 Day 5 (prior to Week 1 data collection commencement) and Week 2 Day 3 (mid-intervention).

### Statistical analysis

A statistical analysis plan will be completed prior to database lock. A participant will be deemed to have not achieved a good outcome if withdrawal is for trial-related reasons (eg, intervention load). A participant will be replaced if withdrawal is for non-trial related reasons (eg, COVID-19). An independent (LO) member will prepare all data summaries for interim and final analyses. Two people will review interim data ([name] content expert and LC statistical expert), protocol deviations and file notes against a priori defined rules to rate each binary item of the composite primary outcome as achieved or not. For efficacy, the change between baseline and post-intervention is calculated for each priority outcome to determine if there is improvement or decline at or beyond the predefined outcome-specific threshold. The first binary item is considered achieved by a participant if at least one priority outcome improves beyond the predefined threshold. The second binary item is considered achieved if the participant does not decline beyond the threshold for any priority outcome. For feasibility, the proportion of time-on-task is averaged across the intervention administration period (Weeks 1/2/3). The third binary item is considered achieved by a participant if their average time-on-task is ≥75%. For safety, all serious adverse event outcomes are reviewed for intervention relatedness. The fourth binary item is considered achieved by the participant if they have no intervention-related serious adverse event. If all four binary items are rated achieved, then a participant is deemed to have made a good outcome. Recruitment to a given study will continue (up to a maximum of n=40) if sufficient participants achieve a good outcome on the single binary composite primary outcome at interim (see figure 1). A study will be stopped if insufficient participants achieve a good outcome at interim. Online supplemental A provides an interim analysis template. All secondary outcomes will be reported at baseline, post-intervention and baseline-post-intervention change (median, SD).

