**Methods and analysis:**

This is an adaptive Phase IIa master protocol umbrella design that includes four simultaneous Bayesian Optimal Phase II studies to evaluate individual UPLIFT interventions against prespecified objective performance criteria. The intervention is upper limb and language training at 2 or 4 hours/day, 5 days/week for 4 weeks, delivered either in person (severe stratum) or via telerehabilitation (mild–moderate stratum). Up to 160 adult participants will be recruited across six metropolitan/regional university or healthcare hubs spanning five Australian states. Baseline and post-intervention assessments are blinded. A promising response is defined as a composite binary outcome combining indicators of promise of efficacy, safety and feasibility. For each UPLIFT intervention, the proportion of participants with a promising response will be monitored at three equally spaced, predefined interim stopping points and one final analysis point (n=40 participants/study). An intervention will be stopped if too few promising responses are observed.

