### Primary outcome

A single binary composite primary outcome (achieved good outcome: yes or no) will be applied to define a good outcome. A good outcome is comprised of four binary items that are achieved at an individual participant level:

Improvement at or beyond the predefined outcome-specific threshold on at least ONE priority outcome, ANDNo deterioration on ANY priority outcome beyond the predefined threshold, ANDGreater than or equal to 75% time-on-task of the allocated dose target across the intervention administration phase, ANDNo serious adverse event related to the intervention.

The UPLIFT trial executive identified four priority outcomes based on psychometric properties and international consensus statement recommendations including the Stroke Recovery and Rehabilitation Roundtables^18^ and Research Outcome Measurement in Aphasia.^19^ Published literature informed group discussion and final selection of a corresponding predefined priority outcome-specific threshold:

Fugl Meyer Upper Limb (impairment): change greater than or equal to 5.25 points.^20^Box and Block Test (activity): change greater than or equal to 5.5 blocks.^21^Western Aphasia Battery-Revised Aphasia Quotient (impairment): change greater than or equal to 5 points.^22^Communicative Effectiveness Index (CETI, activity): change greater than or equal to 10.37 points.^23^

All priority measures are performed by the participant except for the CETI. The CETI is completed by a caregiver, family member or partner of a person with aphasia to assess their functional communication abilities in everyday situations. Post-intervention CETI scoring is independent of baseline score knowledge. If a participant does not have an appropriate person to complete the CETI, the remaining three priority outcomes will only be used to inform good outcome achievement.

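### The 75% time-on-task item of the primary outcome is scored on three weeks, but the dose target it refers to runs over four, and the article numbers the treatment weeks in two ways

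*Protocol article*

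**What the plan says.** The Primary outcome section makes a good outcome depend on four items that must all be met. The third, the only feasibility item, is at least "75% time-on-task of the allocated dose target across the intervention administration phase". That section gives no number of weeks.

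The Statistical analysis section turns the item into a scoring rule: "the proportion of time-on-task is averaged across the intervention administration period (Weeks 1/2/3". The cut-off is applied to that average: "The third binary item is considered achieved by a participant if their average time-on-task is ≥75" per cent.

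Elsewhere the treatment lasts four weeks. The abstract describes "upper limb and language training at 2 or 4 hours/day, 5 days/week for 4 weeks". The Intervention section says "Over 4 weeks, a minimum of 20 (of total 80) sessions each of upper limb, language and integrated treatment are provided". Table 1 puts the intervention and the dose recording in Weeks 1 to 4, marks dose recording as contributing to the primary outcome, shows Week 0 as baseline, and times the post-intervention assessment from Week 4 Day 5. Table 2 allows "Completion within a minimum of 4 weeks and maximum of 5 weeks", that is, 20 to 25 weekdays.

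Two places point to another numbering. The Intervention section has goals and routines set in the first session of Week 0. The Fidelity section counts as one of two video-recorded intervention days "Week 0 Day 5 (prior to Week 1 data collection commencement"; the other is Week 2 Day 3, described as mid-intervention.

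**The concern.** The item is defined against the allocated dose target but scored over a window one week shorter than the period in which that dose is delivered. If Table 1's numbering holds, the last treatment week is unscored; if treatment starts in Week 0, the first week is. Either can differ from the other three: tolerance problems may show early, and fatigue or falling attendance late.

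All four items must be met, so the result on this one can decide whether a participant counts as a good outcome. Those counts drive the stop or continue decision at n=10, 20 and 30 and the final call at n=40 in each of the four studies. A primary outcome that one document defines in two ways leaves the two raters without a single rule to apply.

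**Working it through.** **Inputs.** Dose: 2 or 4 hours/day, 5 days/week, 4 weeks (abstract). Sessions: 80, four per day, of 30 or 60 minutes (Intervention; Table 2). Delivery: 20 to 25 weekdays (Table 2). Scored window: Weeks 1/2/3 (Statistical analysis). Design: rates 0.5 vs 0.7, alpha 0.05, power 0.8, looks at 10, 20, 30 and 40 (Sample size calculation).

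**1. The plan's own figure.** With n=40 and 26 or more good outcomes required, a single-stage exact test has alpha 0.0403 and power 0.807. A search over BOP2 rules (assumed Beta(0.5, 0.5) prior, four looks) gives stopping at ≤3/10, ≤9/20, ≤15/30 and ≤25/40, with alpha 0.040 and power 0.804. So 40 per study is reproduced. The boundaries are re-derived, because the figure with the decision logic is not shown in the text at hand.

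**2. Share of the dose not scored (20-day schedule).**
- Days: (20 − 15)/20 = 25%.
- Sessions: (80 − 60)/80 = 25%.
- Hours: 10 of 40 at 2 hours/day, or 20 of 80 at 4 hours/day, both 25%.

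The share is the same whether Week 4 or Week 0 is left out. If delivery runs to 25 weekdays, up to (25 − 15)/25 = 40% of the weekdays fall outside a three-week window.

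**3. Which numbering the text supports.**
- Two recorded days are called 10% of the duration: 2/20 = 10%, with a Week 0 day counted as one of the two. This fits Weeks 0 to 3. A Week 0 of five days added to Weeks 1 to 4 would give 2/25 = 8%.
- Week 2 Day 3 is day 8 of 15 in Weeks 1 to 3, the exact middle. It is day 8 of 20 in Weeks 1 to 4 and day 13 of 20 in Weeks 0 to 3. So it fits a three-week window best and does not separate the two four-week numberings.
- Table 1 and its Week 4 Day 5 anchor support Weeks 1 to 4.

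The text does not settle the matter.

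**4. When the item result changes.** Let m be the mean over the scored weeks and w the unscored week. The four-week mean is (3m + w)/4, which reaches 75% when w ≥ 3 − 3m (as proportions).

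| m | w below which a pass becomes a fail |
|---|---|
| 80% | 60% |
| 85% | 45% |
| 90% | 30% |
| 100% | never |

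- Pass as scored, fail over four weeks: (3 × 80 + 55)/4 = 73.75%.
- Fail as scored, pass over four weeks: (3 × 70 + 95)/4 = 76.25%.

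**5. How often (assumed inputs, not in the article).** Simulated weekly values used mean time-on-task 75 to 90%, between-person SD 5 to 10 points and week-to-week SD 5 points.
- No drop in the unscored week: 0.1 to 4.0% pass wrongly and 0.2 to 4.0% fail wrongly, roughly balanced.
- A 10-point drop: about 1 to 17% pass wrongly and at most 0.2% fail wrongly.

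These rates are for the item alone. The composite changes only for participants who meet the other three items.

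**6. Sensitivity of the decision (illustration only).** A net 2 of 40 recorded wrongly shifts the good-outcome rate by 2/40 = 0.05. If a true 0.50 is recorded as 0.55, the chance of declaring promise rises from 0.040 to 0.131. If a true 0.70 is recorded as 0.65, it falls from 0.804 to 0.568.

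**The case against.** The strongest reply is that Weeks 1 to 3 is deliberate. The Primary outcome section names a phase without fixing its length, and the Statistical analysis section, using almost the same term, may simply define it. Treatment appears to begin in Week 0, before data collection. On that reading Week 0 is an unscored lead-in, and the fault lies in Table 1's labels. This stands as a possibility. It does not remove the conflict: Table 1 would then be wrong about where treatment and dose recording fall, the scored target would be 60 sessions rather than 80, and no section says that a treatment week is excluded.

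A reader might infer three stronger things that the article does not support.

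- That participants are being misclassified. If Weeks 1 to 3 is the intended window, nobody is misclassified against it; otherwise, only those whose unscored week carries the mean across 75%. The extreme case of three weeks at 75% and one at 0% is partly covered already: trial-related withdrawal counts as not achieving a good outcome, other withdrawals are replaced, and missed days may be made up within 25 weekdays.
- That unattended sessions drop out of the average. The Primary outcome section ties the item to the allocated target, and the raters use prespecified rules that are not shown. Nothing says missed sessions are excluded.
- That the false-positive rate is inflated. Without a drop in the unscored week the errors roughly balance, and the article gives no adherence data.

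**Conclusion.** The inconsistency holds. The scoring rule for one item of the primary outcome covers three weeks, while the dose it is measured against covers four, and the article uses two incompatible week numberings. On the 20-day schedule 25% of the dose is unscored under either numbering; a five-week delivery could leave out more. Participants can therefore be classified differently from the stated definition, in either direction, when the unscored week moves the mean across 75%. Those with similar adherence in every week are unaffected, as is the sample size of 40 per study.

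Frequency and direction are unknown. The simulated rates rest on assumed means and SDs, and the changes in the chance of declaring promise rest on an assumed net shift of 2 in 40; neither is a forecast. The point deserves correction because it concerns the definition of the primary outcome and feeds every interim decision.

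**What to change.** 1. Reconcile the abstract, Primary outcome, Table 1, Intervention, Table 2, Fidelity and Statistical analysis sections. State which weeks form the administration phase, whether Week 0 counts, and how a fifth week is treated.
2. Define the item once: total minutes on task divided by the allocated minutes of all planned sessions in that phase, with missed or shortened time counted as zero. For 80 sessions the denominator is 80 × 30 = 2,400 or 80 × 60 = 4,800 minutes.
3. If one week is a prespecified unscored lead-in, say so in the Primary outcome section and Table 1, and state the reduced target of 60 sessions (60 × 30 = 1,800 or 60 × 60 = 3,600 minutes).
4. Re-score participants already rated only if the reconciled, prespecified definition covers all four weeks. Otherwise keep the Weeks 1 to 3 scoring and report the four-week version as a sensitivity analysis. Re-scoring regardless could change a prespecified primary outcome after interim data have been seen.

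The cost is a wording amendment and possibly a slightly lower pass rate on this item. Session-level dose is already recorded in REDCap. If the unscored week proves to be Week 0, first confirm that its dose was recorded, since the Fidelity section places it before data collection; unrecorded time must not be scored as missed.

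### The time-on-task item of the primary outcome is scored over Weeks 1 to 3, but the intervention it is defined on lasts four weeks, and the week numbering is inconsistent

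*Protocol article*

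**What the plan says.** A good outcome requires four items, all of which must be met. The third is feasibility. The Primary outcome section sets it at no less than "75% time-on-task of the allocated dose target across the intervention administration phase". The Statistical analysis section gives the working rule: "the proportion of time-on-task is averaged across the intervention administration period (Weeks 1/2/3"), followed by "The third binary item is considered achieved by a participant if their average time-on-task is ≥75"%.

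Other parts of the article describe a longer intervention:

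- Abstract: "upper limb and language training at 2 or 4 hours/day, 5 days/week for 4 weeks".
- Intervention section: "Over 4 weeks, a minimum of 20 (of total 80) sessions each of upper limb, language and integrated treatment are provided".
- Table 2: "Completion within a minimum of 4 weeks and maximum of 5 weeks", and "Monday to Friday; minimum 20 weekdays, maximum 25 weekdays".
- Table 1: intervention and dose recording stand under Weeks 1–4, dose recording is marked as feeding the composite, and post-intervention assessment is timed from Week 4 Day 5.

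The week labels also differ. Table 1 has Week 0 as baseline. The Intervention section puts goal setting in a first session in Week 0. The Fidelity section counts Week 0 Day 5 as one of two recorded intervention days, says it comes before data collection starts in Week 1, and calls the other recorded day "Week 2 Day 3 (mid-intervention").

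**The concern.** The definition and the scoring rule name almost the same period, but only the scoring rule puts weeks on it, and it lists three. The remaining treatment week never enters the rating, and neither does any extension towards 25 weekdays. Under Table 1 numbering the unscored week is the last, where fatigue and missed sessions would show. Under the Week 0 numbering it is the first, where initial tolerance would show.

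All four items must be met, so a wrong rating on this one can change a participant's good-outcome status. Those counts drive the stop or continue decisions at 10, 20 and 30 participants and the final decision at 40, in each of the four studies. Feasibility is a stated purpose of this Phase IIa trial. A conclusion that a four-week dose is feasible would rest on three weeks of it, and two published rules could classify the same person differently.

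**Working it through.** **1. Length of the intervention.** Table 2 gives four sessions a day, Monday to Friday. 4 sessions × 5 days × 4 weeks = 80 sessions, which reproduces the total in the Intervention section. Three weeks would give 4 × 5 × 3 = 60. At 30 or 60 minutes a session, 80 sessions are 2,400 minutes (2 h/day) or 4,800 minutes (4 h/day).

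**2. Does the Week 0 numbering remove the conflict?** Suppose treatment runs over Weeks 0–3. The Fidelity section says its two recorded days are 10% of the duration. 2/20 = 10%, while 2/15 = 13.3%. The duration is therefore 20 days and Week 0 belongs to it. Scoring Weeks 1–3 still covers 15 of 20 days.

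| Numbering | Treatment weeks | Scored | Not scored |
|---|---|---|---|
| Table 1 | 1, 2, 3, 4 | 1, 2, 3 | 4 |
| Intervention and Fidelity sections | 0, 1, 2, 3 | 1, 2, 3 | 0 |

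**3. When the two rules disagree.** Let s be the mean percentage of allocated time on task in the three scored weeks and u the percentage in the other week, with equal weekly allocation. The four-week figure is (3s + u)/4, and it reaches 75% when u ≥ 300 − 3s.

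| s | u | Four-week figure | Weeks 1–3 rule | Four-week rule |
|---|---|---|---|---|
| 75% | 50% | (225 + 50)/4 = 68.75% | achieved | not achieved |
| 80% | 0% | (240 + 0)/4 = 60% | achieved | not achieved |
| 72% | 88% | (216 + 88)/4 = 76% | not achieved | achieved |

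The reverse error needs s below 75% and, because u cannot exceed 100%, s of at least (300 − 100)/3 = 66.7%.

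**4. Limiting case.** With s = 75% and u = 0%, the four-week figure is 0.75 × 3/4 = 56.25%. That is 1,350 of 2,400 minutes or 2,700 of 4,800 minutes, against 1,800 and 3,600 minutes needed for 75%. It assumes that missed sessions count as zero and that 15 of the 20 treatment days fall in the scored weeks. If the days were spread over five weeks and 12 fell in Weeks 1–3 (an assumption), the figure would be 0.75 × 12/20 = 45%.

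**5. Design figures, for context.** The decision boundaries are in a figure that is not shown. A reconstructed rule requiring at least 4/10, 10/20, 16/30 and 26/40 good outcomes gives, by exact sequential binomial calculation, a pass probability of 0.0398 at a true rate of 0.50 and 0.8035 at 0.70, in line with the stated alpha of 0.05 and power of 0.8. The sample size is unaffected. What can change is who counts as a good outcome.

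**The case against.** The strongest reply is that the Statistical analysis section simply specifies what the Primary outcome section leaves open. The definition gives no length for the phase, and the scoring rule then supplies it. Week 0 would be a set-up week before dose data collection begins. The label on the second recorded day fits this, since Week 2 Day 3 is day 8 of 15, the exact middle of Weeks 1–3. So the window may be deliberate. That stands as a possibility, but the article does not say so, Table 1 contradicts it, and the Fidelity section's own 10% makes Week 0 part of a 20-day dose. A deliberate three-week window would still have to appear in the definition.

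Several points limit the size of the problem, and they stand:

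- A reader might infer that people with 56% of the dose will commonly be passed. The documents do not support that. Trial-related withdrawal is rated as not a good outcome and other withdrawals are replaced, so the case needs someone who remains in the trial with an empty unscored week. Short sessions also trigger a file note, and raters review file notes against rules that are not shown.
- The 56.25% depends on the denominator. If time on task is averaged over delivered sessions only, missed sessions do not enter and this figure does not apply.
- A reader might also infer a large rise in false promising calls. Under the reconstructed rule, a net gain of 5 percentage points in good outcomes at a true rate of 0.50 would raise the pass probability from 0.040 to 0.131, and a net gain of 1 point would raise it to 0.052. No document gives the size or even the direction of a net shift. The error runs both ways, and affected participants must also meet the other three items. These figures are illustrative only.

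**Conclusion.** The inconsistency is real and lies in a stated scoring rule for the primary outcome. Under either week numbering, one of four intervention weeks (a quarter of the 80 sessions) is outside the rating of the third item, and the definition and the rule can disagree in both directions. The 68.75% and 76% examples assume equal weekly allocation. The 56.25% figure is a limiting case that also needs missed sessions to count as zero.

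The article does not establish that the three-week window is a slip, which week is left out, or whether dose was recorded in that week. It gives no basis for a numerical claim about the trial's error rate.

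**What to change.** Reconcile the Primary outcome, Intervention, Fidelity and Statistical analysis sections and Table 1 on which weeks form the intervention administration phase. Use the same weeks in the numerator and in the allocated-dose denominator of the third item.

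- **If dose was recorded in all four weeks, as Table 1 schedules:** score the item over the whole phase, including any extension to 25 weekdays. Apply this to every participant, including those already rated, by a rule fixed without regard to interim results, and report each rating that changes.
- **If one week is deliberately unscored or was not recorded:** say so in the definition of the item and limit the feasibility conclusion to the three scored weeks.

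In the first case the cost is a short wording change and a re-run of one calculation on dose records already scheduled. In the second it is wording and a narrower claim. If the unscored week is Week 0, the Fidelity section leaves it doubtful that dose data exist for it, so re-scoring may not be possible. The main drawback is that some ratings may change after interim looks have taken place, which must be disclosed.
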